### 2.10. Assignment of Intervention

The chronological order in which a CSPS crosses over to the intervention will be randomized by a statistician at the Institut Pasteur, Paris, using the STATA^®^ version 15.0 (StataCorp, College Station, TX, USA). To minimize the imbalance between the intervention period and the control period, stratification will be performed by the districts (Dafra, *n* = 8; and Dô, *n* = 16). The list of the CSPS with its order will be kept in Paris, and will only be accessible by the study statistician. The intervention start date of each CSPS will be concealed from all the investigators, healthcare workers, and study participants, except the statistician. Two weeks prior to the date of the crossover from the control to the intervention, the statistician will inform the investigators about the next CSPS that will start the intervention. The study coordinator will then notify this CSPS of the intervention start date. This will ensure sufficient time for the delivery of the vaccines to the next CSPS and for the healthcare workers in this CSPS to be ready to start administering HepB-BD.

While a CSPS is in the control period, nobody will know when the intervention will begin in this CSPS. However, once CSPS has crossed over to the intervention, both the investigators and the healthcare workers in this CSPS will know that HepB-BD is now available and given in this CSPS. To limit the risk of selection bias during the enrolment of study participants, healthcare workers will inform pregnant women about the possibility of their child being vaccinated at birth, in the same way during the control and intervention period. However, despite such a precaution, if the pregnant woman spontaneously asks about the allocation status of the CSPS, the healthcare workers will tell her whether the intervention has already been assigned to this CSPS or not.

### 2.11. Data Management

At enrolment, a study identification number will be assigned to each woman. The anonymized data will be collected in a paper CRF at the CSPS, transferred to the research center at the Centre Muraz, and a double entry will be made in an electronic CRF built in the REDCap application [39]. The database will be developed and managed by the study statistician at the Institut Pasteur. All modifications made in the database will be registered according to the Good Clinical and Laboratory Practice (GCLP). Access to the final trial data and dissemination policy will be defined by the scientific committee of the NéoVac project. The final trial results will be presented at the local steering committee, and communicated with the local healthcare workers, civil societies, the Ministry of Health in Burkina Faso, the WHO country office, and the funders of the study.

### 2.12. Statistical Methods

Using an intention-to-treat analysis involving all mother–child pairs included in the study, the impact of introducing monovalent hepatitis B vaccines at birth on the risk of MTCT will be estimated by comparing the proportion of children positive for HBsAg at the age of 9 months between two groups: children born before the introduction of HepB-BD into their CSPS (control arm) and those born after their CSPS begins HepB-BD (intervention arm), regardless of whether or not they have received HepB-BD according to the assignment of the intervention to their CSPS. Our primary analysis will be “complete case analysis” excluding those with missing outcomes as it is unlikely that maternal HBV infection, the leading factor for the vaccine failure, is related with a loss to follow-up [40,41]. We will also conduct a sensitivity analysis with an extreme assumption that all those lost to follow-up were infected with HBV.

A per-protocol analysis will also be performed by restricting the analysis to children born before the introduction of HepB-BD into their CSPS and not having received HepB-BD, or to those born after the introduction of HepB-BD into their CSPS and who have received HepB-BD. To account for the calendar time and for the correlations between individuals within the same cluster, a logistic regression model with a random effect for clusters and a fixed effect for each step will be fitted [25]. All the analyses will be performed using STATA^®^.

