### 2.9. Power Calculation

The power calculation was made for the primary endpoint: the prevalence of positive HBsAg in infants aged 9 months. The study will be carried out in the rural areas of the Dafra health district (8 CSPSs covering approximately 46,000 inhabitants) and Dô health district (16 CSPSs covering approximately 154,000 inhabitants) (Figure 2). At each step, we will have a 3-week interval to allow sufficient time to include the number of participants required per CSPS and per period. To obtain the highest possible statistical power, one cluster will be randomized for each step. The following assumptions were made:(a)The average number of live births in a catchment area covered by each CSPS is about 22 per month.(b)Infant death or lost to follow-up occurs in 10% of children by the age of 9 months.(c)The prevalence of HBsAg in pregnant women (P_HBsAg_) is estimated at 10%, but it can vary from 5% to 15% between the clusters [34].(d)The prevalence of HBeAg in HBsAg-positive pregnant women (P_HBeAg_) is estimated at 15%, but it can vary from 10% to 20% between the clusters [35].(e)With three doses of the pentavalent vaccine (8-12-16 weeks) without timely administration of HepB-BD, the risk of MTCT from HBsAg-positive and HBeAg-positive pregnant women (R_HBeAg-pos_) is 60% [20,36], and the risk from HBsAg-positive and HBeAg-negative pregnant women (R_HBeAg-neg_) is 5% [35].(f)With the timely administration of HepB-BD followed by three doses of pentavalent vaccine, the risk of MTCT from HBsAg-positive and HBeAg-positive pregnant women (R_HBeAg-pos-BD_) is 20% [18], and the risk from HBsAg-positive and HBeAg-negative pregnant women (R_HBeAg-neg-BD_) is 0% [35,37].

Using assumptions (a) and (b), the number of children evaluated at 9 months of age in each observation period (3 weeks) in each cluster (CSPS) was estimated at:*n* = (Average number of live births/CSPS/month) × (1 − lost to follow-up) × (3/4 weeks) = 14.8

Using assumptions (c), (d), (e), and (f), the incidence of HBV infection among the infants aged 9 months in the intervention (π_1_) and the control (π_0_) was estimated at:π_0_ = P_HBsAg_ × P_HBeAg_ × R_HBeAg-pos_ + P_HBsAg_ × (1 − P_HBeAg_) × R_HBeAg-neg_ = 1.33%
π_1_ = P_HBsAg_ × P_HBeAg_ × R_HBeAg-pos-BD_ + P_HBsAg_ × (1 − P_HBeAg_) × R_HBeAg-neg-BD_ = 0.30%

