The coefficient of variation (CV) of the incidence of HBV infection in infants aged 9 months between control clusters (control observation periods) should be determined by the variation in the prevalence of HBV among pregnant women across the clusters. The prevalence of HBsAg in pregnant women is estimated to vary by a maximum of ±5% (5–15%), and the prevalence of HBeAg in HBsAg-positive pregnant women to vary by up to ±5% (10–20%) between the clusters. Consequently, the incidence of HBV infection in infants aged 9 months in the control periods would vary between 0.53% and 2.40% according to the CSPS, with a maximum variation of 1.07% around the estimated average of π_0_ = 1.33% (i.e., π_0_ ± 2SD = 1.33% ± 1.07%). The CV, the ratio of the standard deviation (SD) to the mean, was then estimated to be 0.40 in this study. Using the formula for the power calculation of the stepped wedge cluster randomized controlled trial [38], the study will have an 84% power to demonstrate that the intervention can reduce the incidence of HBV infection in infants aged 9 months, with a significance level of 5%. This corresponds to the inclusion of approximately 8500 mother–child pairs in a recruitment period lasting for 75 weeks (24 steps × 3 weeks + 3 weeks for the last period). Alternative scenarios were considered by varying the number of infants evaluated at the age of 9 months per cluster per period for the same number of participating CSPSs (Figure 5). This shows that the sample size of 13 children aged at 9 months/cluster/period provides a power of 80%.

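### The one stated check on missing outcomes counts every lost infant as infected in both arms, so on the plan's own figures it is usually non-significant even when the vaccine works as assumed

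*Protocol article*

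**What the plan says.** Section 2.12 (Statistical Methods) compares HBsAg positivity at 9 months between infants born before and after their health center started the birth dose. The model is a logistic regression with a random effect for center and a fixed effect for each step. The primary analysis is complete case, "excluding those with missing outcomes as it is unlikely that maternal HBV infection, the leading factor for the vaccine failure, is related with" loss to follow-up. One check on that choice follows: "We will also conduct a sensitivity analysis with an extreme assumption that all those lost to follow-up were infected with HBV". The text makes no distinction by arm.

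Section 2.9 (Power Calculation) gives the scale of the problem: "Infant death or lost to follow-up occurs in 10% of children by the age of 9 months". The control risk is the "estimated average of π_0_ = 1.33" percent, and the intervention risk is 0.30%. In the model behind these risks, only HBsAg-positive mothers transmit. Their prevalence "is estimated at 10%, but it can vary from 5% to 15% between the clusters".

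**The concern.** A sensitivity analysis for missing outcomes should show how far the conclusion depends on what is unknown. Here the outcome is rare (about 1% or less) and the expected missingness is about ten times as common. If every missing outcome is set to positive, most of the events analysed record whether the infant came back, not whether the infant was infected.

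Two consequences follow.

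- With equal loss in both arms, the same large block of events is added to each side and the contrast is diluted. A vaccine that works exactly as planned would usually give a non-significant result in the only stated check, and that could be read as a failure of robustness.
- With unequal loss, the size and direction of the result depend heavily on retention.

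The complete-case choice does need a real check. Its stated justification is that maternal infection is unrelated to loss. The outcome, however, is measured at the routine 9-month vaccine visit (section 2.8.3), and infants who miss that visit may also have missed earlier doses.

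**Working it through.** **Inputs (section 2.9).** 22 live births per center per month; 10% death or loss; 24 centers; 25 periods of 3 weeks; between-center CV 0.40; 5% significance level (two-sided assumed). The control risk is 0.10 × 0.15 × 0.60 + 0.10 × 0.85 × 0.05 = 1.325%. The intervention risk is 0.10 × 0.15 × 0.20 = 0.30%.

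**1. Reproducing the stated power.** For this layout (one center per step, 300 control and 300 intervention cells), the Hussey–Hughes variance is

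Var = 24σ²(σ² + 25τ²) / (2300σ² + 29900τ²),

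where σ² is the variance of a cell mean and τ is the between-center SD. With σ² = 0.01325 × 0.98675 / 14.8 and τ = 0.40 × 0.01325 = 0.0053, the SE is 0.00342. Then z = 0.01025 / 0.00342 = 3.00 and power is 85.0%, against the stated 84%. At 13 infants per cell the formula gives 80.9%, against the stated 80%. The plan's figure is reproduced.

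**2. The same contrast after imputation, 10% loss in both arms.**

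- Control: 0.10 + 0.90 × 0.01325 = 11.19%
- Intervention: 0.10 + 0.90 × 0.003 = 10.27%
- The odds ratio moves from 0.22 to 0.91, and the risk difference from 1.025 to 0.92 points.

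**3. Imputed against observed infections.** Enrolled infants per cell are 22 × 3/4 = 16.5, so 600 × 16.5 = 9,900 are enrolled, 990 lost and 8,910 evaluated. Observed infections are 4,455 × 1.325% + 4,455 × 0.30% = 59.0 + 13.4 = 72.4. The ratio is 990 / 72.4 = 13.7, and the imputed share is 990 / 1,062.4 = 93%. The protocol states about 8,500 pairs. If that is the number enrolled, the counts are 850 lost and 62 infections, and the ratio is unchanged.

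**4. Power of the check.** Using the formula of step 1 with 16.5 infants per cell, σ² at 11.19% and τ = 0.9 × 0.0053, the SE is 0.00810, z = 0.009225 / 0.00810 = 1.14 and power is 20.6%. Taking σ² at the mean of the two proportions gives 21.2%. Two simulations of the planned random-intercept model gave 25% (600 trials) and 27% (150 trials); on complete cases the same simulations gave 99% and 97%. If centers also differ in retention (assumed SD 2 to 4.5 points), the formula gives 14–17%.

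**5. Is it a plausible bound?** At the planned risks, about 495 × 1.325% + 495 × 0.30% = 8 infections are expected among 990 lost infants. If every lost infant of an HBsAg-positive mother were infected, there would be 10% × 990 = 99. The rule imputes ten times that number.

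**6. Unequal loss (assumed; the protocol gives a single 10% figure).** With 10% control loss, the planned effect vanishes when intervention loss L satisfies L + (1 − L) × 0.003 = 0.111925. This gives L = 0.108925 / 0.997 = 10.93%, a gap of 0.93 points. Loss of 9% control and 11% intervention gives an odds ratio of 1.12; loss of 11% and 9% gives 0.74.

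**7. The alternative on planning figures.** Lost control infants stay at 1.325% and lost intervention infants are given risk r: RR = (0.9 × 0.003 + 0.1 × r) / 0.01325.

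| r | RR |
|---|---|
| 1.325% | 0.30 |
| 5% | 0.58 |
| 10% | 0.96 |
| 10.55% | 1.00 |
| 13.25% | 1.20 |

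The top value is the mean transmission risk from HBsAg-positive mothers without the birth dose: 0.15 × 60% + 0.85 × 5% = 13.25%. Significance would be lost before RR reaches 1. With the formula of step 1 at 16.5 per cell, the SE is 0.00327, so the expected z falls below 1.96 when r exceeds (0.01325 − 1.96 × 0.00327 − 0.0027) / 0.1, about 4%.

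**The case against.** The strongest reply is that this is a secondary analysis, openly labelled extreme, on which no decision rule depends. The primary estimate and its power do not change whatever it shows, and a reader told that about 10% imputed positives are set against about 1% observed can discount it. That stands, and it is why the point is not rated higher.

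Other parts of the reply also stand:

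- A reader might infer that the check simply tests retention over time. The model does not support that: a change in retention shared by all centers over calendar time is absorbed by the step effects. In a simulation with loss rising from 7% to 13% in every center alike, the odds ratio stayed at 0.91 and no significant harm appeared in 150 trials. Only a difference that remains between arms after adjustment for step distorts the result.
- A reader might also infer that the check will point to harm or to a false benefit. That needs differential loss, which the protocol neither states nor predicts. Staff know when their center has crossed over (section 2.10), so equal retention is not guaranteed, but the unequal splits remain assumptions. With equal loss, the check only dilutes.
- The count of 990 is an upper figure. It rests on 9,900 enrolled, and the planned 10% includes deaths, which the rule may not impute. At 5% imputed, the odds ratio is still 0.84 and power about 36%.
- Multiple imputation, weighting and separate handling of deaths may be in a statistical analysis plan that is not shown. Their absence from the article is no finding.
- The proposed upper limit of 13.25% is itself extreme and also crosses the null (RR 1.20).

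**Conclusion.** The point holds as a should-fix improvement. With 10% loss in both arms, the stated check turns an odds ratio of 0.22 into 0.91 and adds 13 to 14 imputed infections per observed one (850–990 against 62–72). It has about 20–27% power if the vaccine performs exactly as planned, so a non-significant result would say almost nothing about the complete-case assumption. Giving both arms the same value also means that it does not bound the result against the vaccine. If loss differs between arms after adjustment for step, a gap of about 0.9 points would cancel the planned effect.

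These figures rest on the planning risks, on imputing the whole 10%, and on a two-sided 5% test. Fewer imputed cases would soften the dilution but not remove it. The conclusion does not extend to the primary analysis.

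**What to change.** In section 2.12, replace or supplement the all-infected analysis with a tipping-point analysis under the same logistic model:

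- Hold lost control infants at the observed control risk.
- Raise the assumed risk in lost intervention infants from their observed risk up to 13.25%. State that this limit is extreme: it means that all lost intervention infants have HBsAg-positive mothers and that the birth dose had no effect.
- Report the assumed risk at which the conclusion changes, separately for loss of statistical significance and for the point estimate reaching no effect, and say whether that risk is plausible.

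If the all-infected analysis is kept, report loss by arm beside it and say that it is expected to dilute the effect.

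The cost is about one paragraph of wording and a little more analysis. No new data are needed. The downside is that the result is a range to be judged and not a single figure.

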## 2. Methods

### 2.1. NéoVac Research Program

Neonatal Vaccination against Hepatitis B in Africa study (NéoVac), funded by the Total Foundation, is a research program originally started in 2015 in Senegal, Burkina Faso, and Madagascar, where the hepatitis B vaccination series have been scheduled at 6-10-14 weeks (Senegal and Madagascar) or 8-12-16 weeks (Burkina Faso), without HepB-BD. The aim of the program was to develop and evaluate a strategy to implement the timely administration of HepB-BD in these countries. The program was designed in two successive steps. Step 1, the formative phase, collects epidemiological, anthropological, and economic data in each country in order to develop a locally adapted, sustainable strategy for providing timely HepB-BD within 24 h of birth. This step is followed by Step 2 to evaluate the impact of the strategy to reduce the risk of HBV infection in infants. In Burkina Faso, Step 1 was conducted in Dafra District, Hauts-Bassins Region, in 2016–2017. The epidemiological study found approximately 90% of children born at health facilities, and 86% completed three doses of the pentavalent vaccine. The anthropological study observed that infant vaccination was widely accepted in the communities, and the economic study suggested that the costs of introducing HepB-BD would be relatively low compared to the introduction costs of other vaccines [23]. These results were presented at the steering committee organized by the study investigators in Ouagadougou on 20 Nov 2017, with local healthcare workers, researchers, civil society organizations, the Ministry of Health, and the WHO. Due to a high rate of institutional delivery in the study zone, the committee considered that the administration of HepB-BD in maternity services at health centers would result in good coverage of timely HepB-BD. However, the committee questioned to what extent the addition of HepB-BD would further prevent infant HBV infection. Consequently, the overall objectives of Step 2 were defined as follows: to assess the impact of adding HepB-BD to the current hepatitis B vaccination schedule at 8-12-16 weeks of life on the risk of MTCT, and to evaluate its acceptability among healthcare workers and community members, and its cost-effectiveness.

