#### 2.6.2. Control Period

During the control period, there will be no supply of the monovalent vaccines to the CSPS; therefore, babies born during this period in the catchment area of this CSPS will not receive HepB-BD.

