#### 2.6.3. Interventional Period

Once a CSPS crosses from the control to the intervention period, the monovalent vaccines will be delivered from the district center to the CSPS and healthcare workers will start immunizing newborns. The delivery of HepB-BD will be integrated into a monthly supply chain for the routine infant vaccines. Babies born in the CSPS during the intervention period will receive HepB-BD immediately after birth. Those born at home during the intervention period will receive HepB-BD at the first contact with the CSPS at any time up to the time when the next dose of hepatitis B vaccine is scheduled (i.e., 8 weeks as a pentavalent vaccine) according to the WHO recommendation [21].

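### The per-protocol analysis conditions on receiving HepB-BD, which in practice removes infants only from the intervention period; it is open to selection bias and cannot be read as the effect of a dose within 24 h

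*Protocol article*

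**What the plan says.** Section 2.12 (Statistical Methods) makes intention-to-treat the main comparison. Infants are classed by birth before or after their health centre (CSPS) crossed over, "regardless of whether or not they have received HepB-BD according to the assignment of the intervention to their CSPS".

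A per-protocol analysis is added. Its control side is obtained through "restricting the analysis to children born before the introduction of HepB-BD into their CSPS and not having received HepB-BD". Its intervention side is set in the next clause, which limits it "or to those born after the introduction of HepB-BD into their CSPS and who have received HepB-BD". The model that follows has a random cluster effect and a fixed effect for each step. No individual covariates are named.

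Two other sections determine what this rule does:
- Section 2.6.2 (Control Period): "there will be no supply of the monovalent vaccines to the CSPS".
- Section 2.6.3 (Interventional Period): "Babies born in the CSPS during the intervention period will receive HepB-BD immediately after birth". For home births the section is looser: such an infant "will receive HepB-BD at the first contact with the CSPS at any time up to the time when the next dose" is due, that is, at 8 weeks.

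Section 2.1 reports from the Step 1 study in Dafra District "approximately 90% of children born at health facilities, and 86% completed three doses of the pentavalent vaccine". Under section 2.8.2, visit V2 collects data on childbirth and on whether and when HepB-BD was given.

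**The concern.** The rule reads as two-sided, but only one side can exclude a meaningful number of infants. An intervention-period infant who missed the dose is dropped. A control-period infant who would have missed it cannot be recognised and is kept.

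Missing the dose depends on where the infant is born and when it first reaches the health centre. Non-recipients may therefore also have poorer access to care and fewer pentavalent doses. The per-protocol set does not require pentavalent doses on either side, so infants of this kind can remain among the controls after their counterparts have left the intervention side. Cluster and step effects do not correct for differences between individuals.

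The second issue is what counts as receipt. A dose given at 6 weeks counts the same as one given in the delivery room. Assumption (f) in section 2.9 concerns timely administration, and the Discussion asks whether timely HepB-BD would be enough to eliminate mother-to-child transmission. The per-protocol analysis is the described between-period comparison that conditions on receipt, so readers are likely to take it as the answer. As defined, it is not.

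**Working it through.** **The plan's own figures.** No figure is given for the per-protocol analysis. Those for the primary comparison (section 2.9) reproduce:
- n = 22 × 0.9 × 3/4 = 14.85 (stated 14.8)
- π0 = 0.10 × 0.15 × 0.60 + 0.10 × 0.85 × 0.05 = 1.325% (stated 1.33%)
- π1 = 0.10 × 0.15 × 0.20 = 0.30% (as stated)
- Hussey-Hughes power with 24 clusters, 25 periods, CV 0.40, control-rate variance and two-sided 5% = 85.1% (stated 84%)

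The per-protocol definition affects none of these.

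**Selection.** Let f be the share of infants who do not, or would not, receive HepB-BD. Let r be their infection risk without the dose, relative to recipients without the dose, whose risk is p. The control set keeps both kinds of infant, with risk p × [(1 − f) + f × r]. With no vaccine effect, the intervention set contains only recipients, with risk p. The expected per-protocol risk ratio is

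RR = 1 / [(1 − f) + f × r]

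The documents give neither f nor r, so all values below are assumptions.

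| f | r = 1 | r = 2 | r = 3 |
|---|---|---|---|
| 2% | 1.00 | 1/1.02 = 0.98 | 1/1.04 = 0.96 |
| 5% | 1.00 | 1/1.05 = 0.95 | 1/1.10 = 0.91 |
| 10% | 1.00 | 1/1.10 = 0.91 | 1/1.20 = 0.83 |

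**Late doses.** The planned effect with timely dosing is RR = 0.30/1.325 = 0.23. Let L be the assumed share of recipients dosed late.
- Late doses without benefit: RR = [(1 − L) × 0.30 + L × 1.325]/1.325 = 0.30, 0.38 and 0.46 for L = 10%, 20% and 30%.
- Late doses with half the benefit (risk (1.325 + 0.30)/2 = 0.8125%): RR = 0.27 (0.265), 0.30 and 0.34.

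**Both together.** Take f = 10%, r = 3 and L = 10%, with late recipients otherwise like other recipients.
- Late doses without benefit: 0.833 × 0.304 = 0.253, weaker than the planned 0.226.
- Late doses with half benefit: 0.833 × 0.265 = 0.221, slightly stronger than 0.226.

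The net direction depends on quantities that the documents do not give.

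**The case against.** The strongest points on the other side are these.

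- **Home births are not the non-recipients.** Taking the 10% born outside facilities as f is tempting, but sections 2.6.3 and 2.8.2 let home-born infants be dosed at first contact up to 8 weeks. The same infants cannot be both dropped as non-recipients and kept as late recipients. The true f is unknown and may be well below 10%: enrolment requires antenatal care or delivery at a study health centre, and the outcome requires a 9-month visit. This stands, and it is why the range starts at 2%.
- **Bias is not shown.** It needs r to differ from 1. Section 2.12 names maternal infection as the leading factor in vaccine failure, and section 2.6.4 says antenatal HBV screening is not provided in the study zone, so receipt is unlikely to follow maternal status. This stands in part. Incomplete pentavalent vaccination remains a plausible route, but it is not quantified.
- **The rule is not written for one arm.** It also excludes control infants who received HepB-BD. True; the asymmetry comes from the lack of supply.
- **Catch-up doses are part of the intervention.** Counting them as per protocol is consistent with section 2.6.3. Section 2.12 never claims to estimate a within-24-h effect, and timeliness has its own objective and secondary outcome. This stands. The remaining point is how the result may be read.
- **The analysis plan may add covariates or dose windows.** It may. But section 2.12 already fixes who is in the set, and an analysis plan that follows it inherits the asymmetry.

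**Conclusion.** The concern holds in a limited form. The per-protocol comparison is not randomised, excludes in practice only intervention-period infants, and is open to selection bias. Because receipt includes catch-up doses to 8 weeks, it does not isolate the effect of a dose within 24 h.

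For f between 2% and 10% and r between 2 and 3, all assumed, selection alone would make a null effect look like a risk ratio of 0.98 to 0.83. At r = 1 it does nothing. Once late doses are counted, the net direction is unknown.

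A reader might infer that the estimate is certainly biased in favour of the vaccine, or that a biased figure will enter the economic model. The documents support neither. They do not give the risk of non-recipients, and section 2.17 takes transmission risks with and without HepB-BD from the trial without saying which analysis supplies them.

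This is a worthwhile change to a secondary analysis. The primary intention-to-treat result and its stated power are unaffected.

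**What to change.** Change the per-protocol wording in section 2.12 as follows.

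1. Apply one restriction to both periods: infants born at the health centre. V2 collects childbirth data in both periods, and its timing depends on where the birth took place; confirm that the form records place of birth explicitly.
2. Within that set, compare control infants without HepB-BD with intervention infants dosed within 24 h. Report infants dosed later separately.
3. Label the analysis supportive and non-randomised.
4. Add a compliance-adjusted (instrumental-variable) estimate with the randomised crossover as instrument: the step-adjusted intention-to-treat risk difference divided by the difference in any HepB-BD uptake. If timely uptake is the denominator instead, state the assumption that late doses have no effect. For example, with 90% timely and 10% late at half benefit (assumed), the ratio is (0.90 + 0.10 × 0.5)/0.90 = 0.95/0.90 = 1.06, about 6% too large.

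Cost: a change of wording and a somewhat smaller set for this secondary analysis. Some conditioning on receipt remains among health-centre births, because intervention infants not dosed within 24 h are still set aside. No new data collection is needed if V2 records place of birth, and the primary analysis and sample size stay as they are.
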